## Discussion

Abundant literature has highlighted that inflammation is closely associated with depressive symptoms in patients with MDD [6, 13, 24, 62–65]. Targeting inflammation has therefore become a promising strategy in improving depressive symptoms. Interestingly, numerous studies demonstrate a beneficial effect of anti-inflammatory medications (e.g. NSAIDs or anti-cytokines) on depressive symptoms in patients with MDD [34, 36, 38]. Specifically, administering COX-2 inhibitors such as celecoxib in addition to antidepressant treatment for six or eight weeks improves treatment response and remission in comparison to antidepressant medication alone [48].

According to this literature, identifying individuals with depression and inflammation could therefore help in developing new personalised treatment for MDD. However, to our knowledge, there is no previous study assessing the therapeutic effect of administering anti-inflammatory medication combined with antidepressant medication on the basis of raised inflammatory markers at baseline. Through the RCT we propose, we will be able to investigate the effectiveness of using a simple blood test, before treatment of depression, to guide the use of anti-inflammatory medication as an addition to antidepressant medication in patients with depression and inflammation. Indeed, if the efficacy of augmenting vortioxetine with celecoxib 400 mg is higher in participants with inflammation at baseline compared to participants with no inflammation at baseline, it would be recommended to use this augmentation strategy only in MDD patients with raised inflammation before treatment.

The primary outcome of this study will be MADRS score. It is expected that antidepressant combined with anti-inflammatory medication will reduce MADRS score by 50% from baseline to six weeks (end of treatment) in the ‘Depression with inflammation’ stratum of the study. We also expect that the reduction in MADRS score in the ‘Depression with inflammation’ stratum will be larger among those for whom vortioxetine treatment has been augmented with celecoxib than those in the same stratum receiving vortioxetine and placebo. Furthermore, the MADRS score reduction in the former group will also surpass that achieved by both treatment groups in the ‘Depression with no inflammation’ stratum. CRP level as a secondary outcome measure is expected to be reduced by 50% between baseline and six weeks in the group treated with antidepressant and anti-inflammatory medication in the ‘Depression with inflammation’ stratum of the study and is not expected to change in the group treated with antidepressant only in the same stratum. Similarly, CRP levels are not expected to be changed following both treatments in the ‘Depression with no inflammation’ stratum. Secondary outcome measures also include other inflammatory markers (TNF-α, IL-6 and IL-1β), levels which are expected to be reduced by 50%. In addition, a 50% improvement in cognitive dysfunction, functional measures and workplace functioning is expected. Finally, this study also assesses the safety of the anti-inflammatory celecoxib 400 mg when combined with vortioxetine by measuring potential side effects at each visit.

It is hypothesised that primary and secondary outcome measures will not show a statistically significant difference between participants receiving vortioxetine only and participants receiving vortioxetine plus celecoxib within the ‘Depression with no inflammation’ stratum of the study.

In summary, we anticipate that the results of this trial will allow the development of a decision aid for depression medication, thus improving treatment response and remission, especially in patients suffering from recurrent treatment resistant depression.

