### Recruitment and study design

A total of 200 patients with MDD will be included in the study. Recruitment and treatment take place in the wider Central Adelaide Local Health Network (CALHN), with all participant appointments being held in the Clinical Research Facility in the Health and Medical Sciences Building, Discipline of Psychiatry, University of Adelaide. In addition to this, and to ensure that required numbers of study participants are recruited, people from the general population who meet the inclusion criteria are able to engage with the proposed study, as it is made available through advertisement. Participants are free to withdraw from the study at any time.

The study is designed as a parallel group RCT with a superiority framework, investigating 200 participants with MDD over six weeks in the primary phase followed by a six-month post-RCT follow-up period (Fig. 1). The study proposes to measure the inflammatory marker CRP before the commencement of treatment. Following CRP measurement, study participants are then assigned into one of two study strata based on CRP levels. The first of these study strata is made up of 100 individuals with CRP levels > 3 mg/L (the ‘Depression with inflammation’ stratum) and the second study stratum is an active control, made up of 100 individuals with CRP levels ≤ 3 mg/L (the ‘Depression without inflammation’ stratum). In each stratum, participants are randomly allocated in a 1:1 ratio to augmentation of vortioxetine antidepressant treatment with either celecoxib or placebo. Following six weeks of concomitant administration of celecoxib or placebo with vortioxetine, the celecoxib or placebo is then stopped and the participants are treated with vortioxetine only for an additional two weeks. This allows the opportunity to assess the efficacy of taking vortioxetine alone. While the primary time point is the six weeks in which we compare vortioxetine with augmentation against vortioxetine without augmentation, following the RCT phase, all participants have the opportunity to continue on vortioxetine without celecoxib or placebo for another six months during a post-RCT observational study period.

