### Study sample size

Given a power of 0.95, and an alpha error of 0.05, the study sample size required to detect a change in MADRS of an effect size of 0.25 between baseline and week 6 would be 50 study participants in each of the four groups. This would be a total of 200 study participants (100 participants in the ‘Depression with inflammation’ stratum and 100 study participants in the ‘Depression without inflammation’ stratum; 50 participants in each treatment group, respectively).

We have found in our internal analyses that around 40–50% of individuals have a CRP level of > 3 mg/L, so we expect to be able to recruit 100 participants to the ‘Depression with inflammation’ stratum and 100 participants to the ‘Depression without inflammation’ stratum. The proposed study duration is two years, which will allow time to recruit the required number of study participants.

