## Medications

### Celecoxib

Celecoxib, a cyclooxygenase 2 inhibitor, is a NSAID that has previously been used as an adjunct to antidepressant medication in the treatment of MDD in four trials, with three of these trials exploring six weeks of treatment at 400 mg daily [45–47] and one trial of eight weeks at 200 mg daily [48]. All four of these trials suggested improved antidepressant treatment effects for celecoxib add-on treatment, compared to antidepressants plus placebo. Recent meta-analyses associated celecoxib with an increased efficacy of antidepressant therapy [41]. In particular, augmentation of antidepressant medication with celecoxib showed an improved antidepressant effect by a standard mean difference (SMD) of 0.82 (95% confidence interval [CI]: 0.46–1.17) and without heterogeneity between the studies (I^2^ = 0%) [41]. Furthermore, remission of depression was improved by an odds ratio (OR) of 7.89 (95% CI: 2.94–21.17) and treatment response by an OR of 6.59 (95% CI: 2.24–19.42) by this 6–8-week add-on treatment hence the choice of celecoxib 400 mg for our study. Finally, one trial included peripheral blood tests and found that higher levels of the pro-inflammatory marker IL-6 predicted better antidepressant response to the celecoxib add-on [45]. In the present study, celecoxib 400 mg or placebo is given daily to all the participants at a constant dosage from baseline to week 6.

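### A larger celecoxib effect at CRP > 3 mg/L would not justify recommending augmentation only in that stratum, because it does not show absence of benefit at CRP ≤ 3 mg/L

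*Protocol article*

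**What the plan says.** The Discussion describes how the result would be turned into practice. The condition is that the efficacy of adding celecoxib to vortioxetine "is higher in participants with inflammation at baseline compared to participants with no inflammation at baseline". The consequence is that "it would be recommended to use this augmentation strategy only in MDD patients with raised inflammation before treatment". No size, test or confidence limit is attached to *higher*, and nothing is required of the effect in the low-CRP stratum.

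Three other places bear on this:

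- **Results analysis** plans to assess the interaction between treatment and baseline inflammation. It accepts that the trial has power only for very large interactions. **Objectives** lists the same comparison as secondary objective 2 and says that the trial is not powered for it. Neither section links the assessment to the recommendation.
- **Objectives**, and again the end of the **Discussion**, predict no difference (in the Discussion, no statistically significant difference) between treatments in the low-CRP stratum. This is a hypothesis and is not made a condition of the recommendation.
- **Study sample size** and **Recruitment and study design** fix the precision available: the requirement "would be 50 study participants in each of the four groups", and within each stratum "participants are randomly allocated in a 1:1 ratio".

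**The concern.** The recommendation makes two claims: that CRP modifies the effect of celecoxib, and that patients with CRP ≤ 3 mg/L gain nothing worthwhile from it. The stated condition speaks only to the first. If both strata benefit but one benefits more (a quantitative interaction), the condition is true and the restriction is still wrong.

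This matters because the restriction is the trial's personalised-treatment message, and the Discussion goes on to anticipate a decision aid. Followed as written, the sentence could lead the authors to advise against augmentation in patients for whom the same trial shows benefit.

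**Working it through.** **The plan's own figure.** The sample-size statement is "Given a power of 0.95, and an alpha error of 0.05", "to detect a change in MADRS of an effect size of 0.25 between baseline and week 6", giving 50 per group. The effect-size metric is not stated. Read as Cohen's f = 0.25 for a 1-df effect in four groups, the noncentral F gives power 0.940 at N = 200 (exactly 0.95 needs N = 210), so the figure is approximately reproduced. On that reading it describes the treatment effect over all 200 participants. It does not describe an effect within one stratum.

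**Inputs.** n = 50 per cell and alpha 0.05 come from the protocol. Assumptions: outcome SD = 1 in every cell (no MADRS SD is given, so effects are in SD units), no covariate adjustment and no dropout. All true effects below are assumed for illustration.

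**Precision.**
- Effect within a stratum: SE = √(2/50) = 0.20; 95% CI half-width = 1.96 × 0.20 = 0.39 SD.
- Difference between the two stratum effects: SE = √(4/50) = 0.283 SD.

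**Equal true effects in both strata.**
- *Higher* judged on the two point estimates: P = Φ(0/0.283) = 50%.
- *Higher* judged by a two-sided 5% interaction test, in the direction favouring high CRP: 2.5%.

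**Both strata benefit, one more (assumed 1.0 SD high, 0.6 SD low).**
- Point estimate higher at CRP > 3 mg/L: Φ(0.4/0.283) = Φ(1.414) = 92%.
- Interaction significant: Φ(1.414 − 1.96) = 29%.
- Interaction significant and low-CRP benefit also significant (by simulation): about 18%.

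The last line is the one that matters most. Requiring a significant interaction reduces the problem but leaves trials that show a significant low-CRP benefit and still meet the condition.

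**Does non-significance at low CRP rescue the restriction?** Suppose the rule were *significant at high CRP, not significant at low CRP*. With equal true effects in both strata it would restrict use wrongly in 18% of trials at 0.25 SD, 21% at 0.50 SD and 1.6% at 0.82 SD (by simulation). A low-CRP estimate just short of significance would have a CI running from about 0 to about 2 × 0.39 = 0.78 SD, which is not evidence of no benefit.

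**What a sound criterion can deliver at this size.**
- Interaction power at 0.5 SD: Φ(0.5/0.283 − 1.96) = 42%.
- Interaction needed for 80% power: (1.96 + 0.84) × 0.283 = 0.79 SD.
- Chance that the low-CRP CI excludes a margin m when the true effect is nil: Φ((m − 0.392)/0.20), which is 32% for an assumed m = 0.3 SD and 71% for m = 0.5 SD.

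**The case against.** **It is Discussion prose.** The sentence is conditional, it explains why the trial matters, and nothing in Results analysis uses it. That stands: it is not a formal decision rule. It is, however, the place where the article says how a result would become a recommendation, and the inference it states is invalid as worded.

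***Higher* may mean statistically higher.** An interaction assessment is planned, so a reader who infers that the recommendation would be a coin toss under equal effects goes too far. The 50% holds only if *higher* means a bare ordering of estimates; with the interaction tested at 5% it is 2.5%. The article does not say which is meant. The step to *only* fails on either reading.

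**No difference is predicted at low CRP.** A significant low-CRP benefit would contradict that hypothesis, and the authors might then drop the restriction. This is fair, but the recommendation does not say so, and non-significance with 50 v 50 would not establish absence of benefit.

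**Prior evidence.** The Celecoxib section reports that "augmentation of antidepressant medication with celecoxib showed an improved antidepressant effect by a standard mean difference (SMD) of 0.82", with I² = 0%, and Study sample size says that "around 40–50% of individuals have a CRP level of" > 3 mg/L. A reader might infer that low-CRP benefit is likely. The documents do not support that. I² concerns variation between trials and is silent on modification by CRP within them. The CRP mix of those trials is not given, and a CI for a pooled mean does not bound a subgroup effect. The same section also cites a trial in which higher IL-6 predicted better response. Low-CRP benefit is a possibility that the trial should be able to recognise, and no more than that.

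**A margin belongs in the SAP.** Its value may well sit there. The point here is a stated inference, which the missing SAP does not excuse.

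**Conclusion.** The concern holds as a fault of inference. A larger effect at CRP > 3 mg/L, even with a significant interaction, does not support restricting augmentation to that stratum, and no other section supplies the missing condition on the low-CRP effect. The size depends on assumed effects. At 1.0 and 0.6 SD, about 18% of trials would show both a significant interaction and a significant low-CRP benefit. These figures rest on 50 per cell, SD 1, no adjustment and no dropout; covariate adjustment would sharpen them and dropout would blunt them. The logical point needs none of these numbers. The sentence should be corrected, but this is not a defect in the design or in the primary analysis. Neither a fixed 50% error rate nor a likely benefit at low CRP can be claimed from the documents.

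**What to change.** Reword the Discussion sentence along these lines:

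1. Modification of the celecoxib effect by CRP will be claimed only from the planned treatment-by-inflammation interaction estimate with its CI.
2. A restriction to raised inflammation will be stated only if, in addition, the CI for the celecoxib–placebo MADRS difference at CRP ≤ 3 mg/L excludes a smallest worthwhile benefit fixed before unblinding.
3. Otherwise both stratum effects will be reported with CIs and the CRP finding described as hypothesis-generating.

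The cost is a rewritten sentence and one margin, with no extra patients or data. The downside should be stated openly: the restrictive conclusion becomes hard to reach at this size. Interaction power is about 42% at 0.5 SD, and about 0.79 SD is needed for 80%. With a truly nil low-CRP effect, the CI condition is met about 32% of the time for an assumed 0.3 SD margin and 71% for 0.5 SD. If that is too demanding, the minimum change is to drop *only* and present the comparison of strata as hypothesis-generating, which fits the protocol's own statements about power.

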## Trial status

The trial has commenced recruitment and participant inclusion in November 2017.

If any important changes to the study protocol become necessary, where appropriate, the PI will notify the HREC, trial register, financial sponsor, University and the present journal. The HREC and PI, respectively, have the power to end the study early if the need arises. The trial is subject to audit at any time by the HREC and/or DMC.

## Abbreviations

ANCOVA: Analysis of covariance
CGI: Clinical Global Impression
CNS: Central nervous system
CRP: C-reactive protein
C-SSRS: Columbia Suicide Severity Rating Scale
DSST: Digit symbol substitution test
EWPS: Endicott Work Productivity Scale
FAST: Functioning Assessment Short Test
GI: Gastrointestinal
IFN-α: Interferon-α
IL-1ra: Interleukin-1 receptor antagonist
IL-6: Interleukin-6
LOCF: Last observation carried forward
MADRS: Montgomery–Åsberg Depression Rating Scale
MDD: Major depressive disorder
MDE: Major depressive episode
MINI: Mini-International Neuropsychiatric Interview
MMRM: Mixed model for repeated measurements
NART: National Adult Reading Test
NSAID: Non-steroidal anti-inflammatory drug
OC: Observed case
OR: Odds ratio
PDQ-5D: Perceived Deficits Questionnaire-5D
PI: Principal investigator
RANZCP: Royal Australian and New Zealand College of Psychiatrists
RCT: Randomised controlled trial
SDS: Sheehan Disability Scale
SMD: Standard mean difference
TGA: Therapeutic Goods Administration
TNF-α: Tumour necrosis factor-α
WLQ-25: Work Limitation Questionnaire
